### Primary outcome

Therapeutic equivalence will be assessed by calculating change in mean seated systolic blood pressure (SBP). The minimal clinically important difference (MCID) is the smallest treatment effect that would lead to a change in a patient’s management [32]. Based on the academic literature [33], an average SBP difference of 5 mmHg is accepted as the MCID. A difference of < 5 mmHg in SBP between the two treatments is, therefore, considered to be of no clinical importance. Clinically important differences can be defined using a predefined MCID and confidence interval of the difference of the two treatments [34].

Clinically important differences in mean BP readings between the two treatments can have four interpretations, depending on the relationship of the MCID of the intervention to the point estimate (the best single value of the efficacy of the intervention that has been derived from the study results) and the 95% CI surrounding it [34] (see Fig. 4):

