### Criteria to establish therapeutic equivalence

Absence of a clinically important difference – for therapies to be considered equivalent, not only should the comparison of the efficacies of the two interventions not reach statistical significance, but also the upper limit of the confidence interval should be smaller than the predetermined MCIDEquivalence should be evident in at least in two cycles out of three

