#### Statistical methods

Analysis will be conducted based on BP measurements taken in the last 5 days of each of the six periods. The first 2 days’ BP measurements in each period will be discarded. Based on the academic literature [33], 6 mmHg is accepted as the MCID. Therefore, a SBP difference of ≥ 5 is considered clinically significant. A mean change in evening SBP of < 5 mmHg between the two test medicines in at least two treatment cycles will be considered as representing TE.

Differences in treatment means will be explored graphically, and through the paired Student’s *t* test as appropriate. Significance will be set at *P* < 0.05. The data will also be modeled within a linear mixed-effects modeling framework to account for repeated measures over time such that between- and within-patient variability can be captured (and estimated). If the modeling provides evidence that sources of variability are significant (e.g., possible relationships between the three readings at each morning and evening), then appropriate adjustments built in to the model will be retained. From such a model, population and individual estimates of treatment means can be obtained, and the influence of additional variables. such as treatment order. can be accounted for (if needed). This statistical analysis will be undertaken in the R package.

The type and severity of possible side effects of the study medication and any serious adverse events will be tabulated for individual patients.

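### Statistical methods lets an observed difference below 5 mmHg in two cycles stand as therapeutic equivalence with no confidence interval, in conflict with the protocol's own confidence-limit criterion

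*Protocol article*

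**What the plan says.** All places are in the protocol article.

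- **Primary outcome** sets the margin ("an average SBP difference of 5 mmHg is accepted as the MCID") and judges clinical importance by where the MCID lies relative to the point estimate "and the 95% CI surrounding it". The legend to Fig. 4 rules out an important difference only when the upper 95% limit lies below the MCID.
- **Criteria to establish therapeutic equivalence** sets three conditions: "not only should the comparison of the efficacies of the two interventions not reach statistical significance"; in addition "the upper limit of the confidence interval should be smaller than the predetermined" MCID; and equivalence must be seen in two cycles of three.
- **Statistical methods** states the decision again: "A mean change in evening SBP of" less than 5 mmHg "between the two test medicines in at least two treatment cycles will be considered as representing TE". No confidence interval is mentioned. The same paragraph says "6 mmHg is accepted as the MCID" and then cuts at 5. It adds "Significance will be set at *P* < 0.05" for the paired t test, without tying that test to the equivalence decision.
- **Secondary outcomes** lists evening home SBP as a secondary measure. The Abstract names home SBP, with no time of day, as primary.

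**The concern.** An equivalence claim needs evidence that the true difference lies inside the margin. An observed difference inside the margin is weaker, because it takes no account of sampling error. As written, the Statistical methods sentence is enough by itself to declare equivalence, so it competes with the interval-based criterion.

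With both rules in the text, the more favourable one could be applied once the data are seen. The stakes are practical. Individual study result report hands each result to the patient and physician to decide whether the local drug works. The Discussion says a finding of no difference lets patients take the local product with confidence.

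**Working it through.** **The plan's own figures.** Readings per period: 5 days x 2 occasions x 3 readings = 30, as stated. Enrolment: 30 x 1.10 = 33, as stated. The article gives no SD, SE, power or error rate for the equivalence rule, so there is no operating figure to reproduce. An evening-only endpoint would use 5 x 1 x 3 = 15 readings per period, not the 30 on which Sample size estimation rests.

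**Can the two rules disagree?** Take cycle differences of 4, 4 and 12 mmHg.
- Statistical methods: two of three are below 5, so equivalence is declared.
- Confidence limit: mean = 20/3 = 6.67; SD = 4.62; SE = 4.62/√3 = 2.67; t(2 df, 0.975) = 4.303. The 95% CI is 6.67 ± 11.47, or -4.8 to 18.1. The upper limit is far above 5, so the criterion fails.
- With an interval for each cycle instead, an observed 4 mmHg fails once 1.96 x SE exceeds 1, that is, once SE is above about 0.51 mmHg.
- In the other direction, a precise and significant 2 mmHg difference passes Statistical methods but fails the non-significance condition.

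**How often does the point-estimate rule pass?** Inputs: cut 5 mmHg, two of three cycles, independent cycles, normal errors, and an assumed SE of one cycle's difference (s). The chance that one cycle passes is p = Φ((5-d)/s) - Φ((-5-d)/s). The chance that at least two of three pass is 3p² - 2p³.

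Example at d = 6, s = 5: p = 0.421 - 0.014 = 0.407, and 3(0.1655) - 2(0.0673) = 0.36.

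| True difference d | s=1 | 2 | 3 | 4 | 5 | 6 | 8 |
|---|---|---|---|---|---|---|---|
| 5 mmHg | 50% | 50% | 50% | 49% | 47% | 43% | 34% |
| 6 mmHg | 7% | 23% | 31% | 35% | 36% | 35% | 30% |
| 7 mmHg | 0.2% | 7% | 16% | 23% | 26% | 28% | 26% |
| 8 mmHg | <0.1% | 1% | 7% | 13% | 18% | 21% | 22% |

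**The same rule on the mean of 30 patients.** With an assumed per-patient cycle SD of 8, s = 8/√30 = 1.46. It passes 50% at 5 mmHg, 15% at 6, 2% at 7 and 0.1% at 8. Over assumed cycle SDs of 3 to 8 and between-patient SDs of 0 to 4, it passes about 50% at 5, 0.3 to 21% at 6, at most 5% at 7 and under 1% at 8.

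**A 95% CI wholly within ±5 mmHg (simulated).**
- One patient, paired t on three cycle differences, SD 1 to 5: passes 2.0 to 2.5% at a true 5 mmHg and at most about 1.2% at 6.
- One patient, truly identical products: 96% at SD 1, 49% at 2, 22% at 3, 11% at 4, 6% at 5 and 4% at 6.
- Thirty patients, truly identical products: over 98% at a patient-level SD of 6 and about 82% at 8. At a true 5 mmHg it passes about 2.5%.

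**The case against.** The kindest reading is that the Statistical methods sentence is shorthand for the two-cycle condition in the Criteria section, with the interval requirement understood. That may be what was meant, but the text does not say so and its wording makes the condition sufficient. A separate analysis plan or fuller protocol would not remove the conflict, since both rules are stated here.

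Four points limit how far the concern can be taken.

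- **Size.** A reader might infer that the rule passes non-equivalent products 30 to 50% of the time. That range fits one patient at a true difference of about 5 to 6 mmHg with a per-cycle SE of roughly 3 to 8, which the article does not give. For one patient the rate never exceeds about 28% at 7 mmHg or 22% at 8. Passing half the time at the cut-off is a property of any point-estimate rule.
- **Sign.** A reader might take the missing absolute value to mean that any negative difference passes. This is strained: Primary outcome and Statistical methods both describe the size of a difference between treatments. The Criteria section is itself worded one-sidedly, naming only the upper limit.
- **Two of three cycles.** Both sections share this requirement, so it is not part of the conflict. Combined with a per-cycle interval it makes the test stricter: with the SE known, the pass rate at 5 mmHg is below 0.2%.
- **Cost.** For a single patient, the interval rule rarely declares truly identical products equivalent unless cycle differences vary little. Individual results are a stated aim, so the repair is not merely a matter of wording.

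**Conclusion.** The conflict stands and bears on the primary conclusion. One section requires a confidence limit to clear the MCID, together with a non-significant comparison. Another accepts an observed difference below 5 mmHg in two cycles. They can return opposite answers on the same data.

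At a true difference equal to the 5 mmHg margin, the point-estimate rule passes about 50% of the time for a per-cycle SE up to 3 and 43% at SE 6. A 95% CI rule passes about 2 to 2.5%. At 6 mmHg the single-patient figure is 7 to 36% for SE 1 to 8. Beyond that it falls, most sharply in the 30-patient aggregate.

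The textual conflict needs no assumption. The rates assume normal, independent cycle differences, a two-sided reading of the cut, and SEs and SDs that the article does not supply. The same Statistical methods paragraph adds two further inconsistencies that any repair must settle: evening SBP as the deciding endpoint, and an MCID of 6 mmHg against 5 elsewhere.

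**What to change.** - Remove the Statistical methods sentence as a sufficient criterion.
- State one rule for the aggregate conclusion: the two-sided 95% CI for local minus imported home SBP, from the planned mixed model using all completed periods, lies wholly within plus or minus the MCID. Stating both limits also repairs the one-sided wording in the Criteria section. This rule would replace the non-significance condition, which can fail a small, precisely estimated difference inside the margin.
- Name one primary SBP endpoint, and reconcile the 5 and 6 mmHg MCID values so that one margin appears throughout.
- The two-of-three-cycle requirement may stay as an added consistency check, but not in place of the interval.
- For each patient, report the estimate and CI using the Fig. 4 categories. Label a patient whose interval crosses the margin as inconclusive, not equivalent.

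**Cost.** No new patients or measurements are needed; Trial status reports all 33 enrolled. The chance of declaring equivalence falls. For truly identical products in the 30-patient aggregate, it stays above 98% at a patient-level SD of 6 and is about 82% at 8. For one patient it is about 49% at a cycle-difference SD of 2 and 11% at 4, so many individual reports would be inconclusive.

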## Methods

### Trial design

This is a TE study using N-of-1 trials or tests. Each N-of-1 test will be a randomized, partially blind, multiple-crossover study designed to simulate the routine clinical practice of switching a patient between generic and brand forms of enalapril.

Each N-of-1 trial will consist of three successive 14-day treatment pairs, each pair comprising 7 days of Envas and 7 days of Ena-Denk in random order, taken once daily in the morning. The order of treatments in each treatment pair will be determined by block randomization. Figure 1 shows the study design for a sample arrangement of treatment order. The protocol conforms to the Standard Protocol Items: Recommendations for Interventional Trials (SPIRIT) guidelines [29]. The SPIRIT Checklist can be found in Additional file 1. Figure 2 shows the SPIRIT schedule of enrollment, interventions and assessments [29].

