### Randomization

We will use block randomization, and with a block size of 2, by a statistician at The University of Queensland (UQ). The order in which patients receive drugs will be randomized by computer for each single case, such as BA-AB-BA or AB-BA-BA. The randomization schedule will be sent to a pharmacist who is independent of the study at the ALERT hospital. Prepared study medications will be delivered, stored and dispensed at the AHRI pharmacy unit. Randomization codes will be kept by the ALERT pharmacy. The codes will be broken by the Data Safety and Monitoring Board (DSMB) if safety concerns arise. Figure 3 shows the flow of participants through the trial.

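### Treatment order is adjusted for only if needed, although three randomised pairs cannot balance order within a completer; unadjusted individual and cycle-level results therefore carry a random-sign share of any within-pair period effect

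*Protocol article*

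**What the plan says.** The Trial design section fixes the structure for each patient, with the sequence inside each pair left to chance: "Each N-of-1 trial will consist of three successive 14-day treatment pairs, each pair comprising 7 days of Envas and 7 days of Ena-Denk in random" (the sentence goes on). On how that sequence is set, the same section states: "The order of treatments in each treatment pair will be determined by block randomization". The Randomization section gives the block size ("We will use block randomization, and with a block size of 2") and two example sequences, "such as BA-AB-BA or AB-BA-BA". Both examples split two to one in order.

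The Statistical methods section names three tools.
- Treatment means are compared "through the paired Student’s *t* test as appropriate".
- A linear mixed-effects model is fitted. "From such a model, population and individual estimates of treatment means can be obtained", and the influence of further variables may be included, "such as treatment order. can be accounted for (if needed"). The article gives no criterion for need.
- A mean difference in evening SBP below 5 mmHg "in at least two treatment cycles will be considered as representing TE". The section on criteria for therapeutic equivalence repeats the two-of-three requirement.

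Neither the t test nor the cycle rule is stated with an order term. The section on the individual study result report says that each patient's result goes to the treating physician, for a decision on whether the local product works for that patient.

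**The concern.** The pair is the randomised unit, so order is a design factor. The plan nevertheless treats it as a covariate that may or may not enter the model. Randomisation balances order across the pooled sample but not within one patient, because an odd number of pairs cannot split evenly.

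Individual verdicts are a main product of an N-of-1 series, and averaging over patients does not protect them. If the second week of a pair tends to read lower or higher than the first, for example because patients newly taught to measure at home are still settling in, part of that change is counted as a difference between products. In a single cycle all of it is. An undefined condition for adjustment also leaves a modelling choice open that could be closed in advance.

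**Working it through.** **Inputs from the protocol.** Three pairs per patient (Trial design); blocks of 2, so each pair is AB or BA with probability 1/2 (Randomization); a 5 mmHg threshold and at least two of three cycles (Statistical methods; criteria for therapeutic equivalence); 30 patients plus 10%, 30 × 1.1 = 33 (Sample size estimation). This gives 30 × 3 = 90 to 33 × 3 = 99 pairs. The protocol gives no period effect and no SD of a cycle difference, so there is no figure of its own to reproduce on this point. Both quantities are assumed below.

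**Order balance.** Code a pair s = +1 or −1 by order. Of the 2³ = 8 sequences, the sum S of the three codes is ±1 in 6 and ±3 in 2, and never 0. So P(2:1) = 0.75 and P(3:0) = 0.25, about 0.25 × 33 = 8.25 patients.

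**Share carried.** Write the difference in pair i as d_i = τ + s_i·π, where τ is the product difference and π a constant second-minus-first effect.
- Patient mean: τ + π·S/3, so the shift is π/3 (75%) or π (25%).
- Single cycle: the shift is the whole of π.
- For π = 1, 2, 3 mmHg (assumed), the patient shift is 0.33, 0.67, 1.0 mmHg (2:1) or 1, 2, 3 mmHg (3:0).

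**What does not carry through.**
- A level shift between cycles gives a contrast of 0 in all 8 sequences.
- Unequal pair effects can cancel: effects of 2, 1, 1 give 0 in 2 of 8 sequences.
- With only two cycles analysed, order balances with probability 0.5.
- The expected value of S is 0. The pooled share has SD 1/√90 = 0.105 to 1/√99 = 0.101, which for π = 2 is about 0.2 mmHg.

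**Effect on the two-of-three rule, applied per patient, with τ = 0.** One cycle passes with p = Φ((5−π)/SD) − Φ((−5−π)/SD), and the rule with 3p² − 2p³.

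| SD of cycle difference (assumed) | π = 0 | π = 2 | π = 3 |
|---|---|---|---|
| 3 mmHg | 0.974 | 0.924 | 0.837 |
| 5 mmHg | 0.762 | 0.711 | 0.649 |

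**With a true difference of 6 mmHg and π = 3.** Each cycle has mean 9 or 3 mmHg according to its order.
- SD 3: the pass probability is 0.31 with no period effect. With it, it is 0.02 or 0.84 in the two 3:0 sequences, and 0.13 or 0.59 in the 2:1 sequences.
- SD 5: the corresponding figures are 0.36; 0.11 or 0.65; and 0.24 or 0.46.

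**What adjustment gains.** The mean of (S/3)² is 0.75 × 1/9 + 0.25 × 1 = 1/3. For SD 3 and π = 2, the root mean square error of an unadjusted patient mean is √(9/3 + 4/3) = 2.08 mmHg. With π removed it is √3 = 1.73 mmHg. A simulation of 30 patients, with π estimated from all 90 pairs, gave the same two values and raised the pass rate from 0.924 to 0.975. With no period effect, the adjustment left error and pass rate essentially unchanged (1.73 and 1.72 mmHg; 0.974 and 0.975).

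**Own-data adjustment is not enough.** Within one 2:1 patient, adjusting raises the variance from 0.333 to 0.375 of the cycle variance (+12.5%) and leaves one residual degree of freedom. Within a 3:0 patient, order and product are fully confounded. The period effect has to be estimated across patients.

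**The case against.** The strongest reply has five parts.

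- **The model already allows it.** The mixed model that yields the individual estimates may include order, so only unadjusted results are affected. This stands and limits the point to the optional wording, the t test and the cycle rule.
- **The assumed pattern is demanding.** A constant π in all three pairs needs either a sawtooth or a linear drift of π per period; over five steps, 1 to 3 mmHg becomes 5 to 15 mmHg. Patients are stable and trained beforehand, and the first two days of each period are dropped. Habituation would more likely fade. If it is confined to the first pair, a completer's mean carries one third of it, and the two-of-three rule tolerates one disturbed cycle. This stands too: the tabulated figures are illustrations, not forecasts.
- **It is noise, not bias.** Order is randomised in every pair. This is correct.
- **A common term is imperfect.** It does not remove effects peculiar to one patient, and in 3:0 patients the correction is wholly borrowed. True, but in the simulation it still reduced error when the effect faded or varied between patients.
- **Model terms belong in an analysis plan that is not shown.** This is partly right. The point rests on what the article does state: order is conditional, and the two decision tools are given without it.

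A reader might infer that every individual result is biased by any period effect, or that the analysts will choose the model by its result. The documents support neither. Between-cycle changes cancel, the expected shift is zero, analysts are to be blinded, and the nearby sentence about retaining adjustments concerns sources of variability such as correlated readings.

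**Conclusion.** The point holds in a limited form. In a patient who completes three cycles, unadjusted results carry one third (75%) or all (25%) of a constant within-pair period effect, and each cycle difference carries all of its own pair's effect. This adds random-sign error to individual and cycle-level verdicts. The population estimate is hardly touched, with an SD of about 0.10 times the effect.

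The practical size depends on a period effect and a cycle-difference SD that the documents do not give, and on applying the two-of-three rule patient by patient. For effects of 2 to 3 mmHg and SDs of 3 to 5 mmHg, the pass probability for identical products falls by about 0.05 to 0.14. If the true effect is near zero, nothing is lost in either direction. The change is worth making because it is close to free, not because the trial's overall conclusion is at risk.

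**What to change.** Replace the conditional wording with a fixed model: cycle (pair) nested in patient, treatment, and a fixed term for period within pair that is kept whether or not it is significant. Since habituation may fade, the term may be allowed to differ by cycle. Estimate it from all completed pairs, and take the individual and cycle-level differences used for therapeutic equivalence from this model, not from raw pair differences or an unadjusted t test.

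The cost is one degree of freedom out of roughly 90 to 99 pairs, or three if the term is fitted by cycle, with no new data. The text should state two limits: in patients with a 3:0 order the correction comes entirely from other patients, and period effects specific to one patient are not removed.

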#### Data management

Data that will be generated in this study will be appropriately documented and checked for validity and accuracy. Study data will be managed using the R package. Data from paper CRFs will be double entered into the database by two persons independently so that data will be matched and checked for validity and accuracy before being endorsed for analysis. Problems with incomplete and missing data will be resolved in the following ways. If a patient missed a day of BP measurement, we will provide a mean score for that period. However, if there are more than or equal to 2 days’ data missing, we will not provide a score for that period and that will be indicated in the patient’s report. As per International Conference on Harmonization (ICH) Good Clinical Practice (GCP) guidelines [48], the investigators will maintain information in the study subjects’ records which corroborates the data collected and entered into the CRFs.

## Discussion

The numbers of local pharmaceutical industries that market their products, such as enalapril, without proof of bioequivalence are dramatically increasing. The Ethiopian guideline for registration of medicines states the need for clinical trial evidence on occasions when PK bioequivalence is not applicable. The guideline states that when in-vivo studies using plasma concentration time-profile data are not suitable, a comparative clinical trial then has to be performed to demonstrate equivalence between two formulations. However, as stated in the background, in East Africa including Ethiopia, local generics are marketed without evidence of effectiveness obtained through bioequivalence studies or clinical trials.

By bridging the information gap on bioequivalence, the trial will give rigorous evidence on TE of local enalapril in individual patients. If there is no difference between the two treatments (the hypothesized result), then patients can take the local cheaper medicine with confidence. This trial will also will determine whether aggregated N-of-1 studies are feasible to provide a population level estimate of clinical equivalence for untested generic drugs in resource-limited countries where bioequivalence testing centers are unavailable. If TE is shown, it will encourage the use of cheaper local drugs by enhancing reliance on local pharmaceutical companies.

However, there are a number of challenges in the design and conduct of reliable N-of-1 TE studies. Generally, comparison of drug formulations using TE studies are recommended if the PK approach is not possible [26, 27]. TE studies demonstrate that a test formulation has equivalent efficacy to a reference one. Often times, TE tests using clinical endpoints are less reliable due to lack of clearly defined endpoints and huge variability in the measured parameters [26]. Therapeutic equivalence studies with biomarkers reflecting efficacy endpoints (e.g., BP reduction) are more sensitive than TE studies with clinical endpoints (e.g. survival rates, myocardial infarction and stroke) [26, 27]. Beside, N-of-1 trials are suitable only in chronic conditions where the drugs or interventions that are to be tested have a relatively short half-life [24, 25]. The use of technology (e.g., mobiles, BP machines, etc.) has a significant contribution in standardizing treatment measures. We are comparing antihypertensive effect (maintenance of BP) which is amenable to the use of these reliable technologies.

Patients involved in this trial are not blinded. While double blinding is an ideal option, the need to adapt to local conditions is also very important. Apart from logistic issues (lack of an encapsulation machine locally), keeping the design less complex would make the trial resemble the usual way of switching drugs except that it is pre-planned, randomized and closely monitored [49]. Our method of unblinding of patients and keeping study clinicians and investigators blinded is a compromise between feasibility and minimal potential effects on reported outcomes. The outcome of the study (BP) could be affected more than other possible, but not feasible, outcomes (e.g., serum renin levels). On the other hand, the use of electronic BP devices will help in standardizing the measure. The importance of maintaining blinding is part of patient education that is a routine part of patient preparation for participation in the trial. Study medications are prepared by an independent pharmacy unit. Therefore, study investigators and DSMB members will be blinded. A review of the relevant academic literature found that three N-of-1 papers, including one protocol publication on hypertension, were not fully blinded [22, 23, 49].

